## Methods and design

### Trial design

A crossover randomized trial with three conditions will be carried out. All procedures will take place at the Swedish School of Sport and Health Sciences (GIH) in Stockholm, Sweden. Initially, each participant will attend a familiarization visit either at the laboratory at GIH with parental accompaniment or the researchers will visit the schools.

After the familiarization visit, participants will be assigned 3 experimental days for undergoing 3 different randomly ordered experimental conditions, each consisting of an 80-min sitting exposure. There will be a minimum washout period of 7 days between each visit [51, 52], to reduce carryover effects from the previous condition. Two participants will be tested simultaneously (with a 20-min gap between starting times) to increase efficiency and comfort for the participants. Participants will have a 24-h monitoring and standardization of their physical activity, sleep, and dinner prior to each experimental test day. Participants will receive compensation (600 SEK gift card) for their participation.

### Participants

Researchers will initially contact and visit interested schools in Stockholm and the greater Stockholm region, based on schools that have participated in a previous cross-sectional study at GIH, in order to minimize recruitment challenges. After agreement by teachers and the schools’ principals, consent forms will be sent home with the students to be signed by both parents prior to data collection. Students will then be invited to come to the laboratory at GIH with parental accompaniment for a familiarization session or researchers will visit the schools to introduce the study.

#### Eligibility criteria

Inclusion criteria are children aged 13 to 14 years. Those with ongoing medication that can affect the central or cerebrovascular circulation will be excluded, as well as those who have an ongoing infection, or are unable to apprehend information about the study or how to perform the tests. Students and parents must provide written informed consent prior to study commencement. Participants will be also informed that they may drop out from the study whenever they deem it necessary.

### Familiarization visit

Demographic and other data to describe the individual participant will be collected during the familiarization session including age, gender, height (not if familiarization was performed at the school) and weight without shoes, and a health screening questionnaire for potential contra-indicators. They will also be advised regarding what types of situations during testing that could lead to an immediate discontinuation to ensure safety in the laboratory (i.e., chest pain or similar; difficulties breathing; dizziness, confusion, slowed movements, feelings of sickness, coldness or cold sweaty skin; increase in heart rate not related to increased physical activity intensity; test leader decides to abort; physical or verbal signs of expressed exhaustion; or test equipment breaks). Blood pressure and heart rate will also be measured after 5 min of rest. In order to optimize fNIRS cap fitting, to increase reproducibility of fNIRS cap placement for each subsequent visit, and for head remodeling in future analyses, head circumference, nasion-to-inion, and left and right pre-auricular measurements will be taken, using a tape measure. The cognitive test will also be performed to increase familiarity and reduce practice effects.

A form with choices of food items, provided by Coop Sweden, will also be filled in (i.e., bread [soft or hard]; toppings [butter, cheese, red pepper, or cucumber]; yogurt or sour milk [filmjölk]; muesli or rye cereal; fruit [apple or clementine]), in order to standardize breakfast on experimental days. Additionally, participation in planned organized sport activities or other training will be noted to standardize physical activity the day before the experimental day. This information will also be used in order to determine which consistent weekday the participant would visit the lab, where they would have performed little or the same level of physical activity before each visit.

After the familiarization visit, allocation sequence for the order of experimental conditions will be assigned through individual randomization from a computer-generated random order, equally assigned to every participant. Randomization will be computer-generated by a researcher involved in the study and will be concealed through a password-protected document that will not be revealed until recruitment and the familiarization visit is completed. Researchers cannot be blinded in this type of study design or condition. Researchers within the study will have access to the allocation sequence list and will retrieve the randomization code prior to each experimental day in order to prepare the laboratory equipment.

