#### Cerebral blood flow

The primary outcome measure will be the changes in oxygenated hemoglobin (oxy-Hb) using a non-invasive multi-channel continuous wave fNIRS instrument (portable NIRSport, 8-8 system, with short-separation channels, NIRx Medizintechnik GmbH, Berlin, Germany). The optodes will be positioned over the prefrontal cortex, with data sampled at 7.81 Hz at wavelengths 750 nm and 820 nm, for oxy-Hb and deoxygenated hemoglobin (deoxy-Hb), respectively. The fNIRS cap has 8 LED light sources and 8 detectors placed according to the standard 10–20 system, with a source-detector separation distance of 3 cm (Additional file 2). The eighth detector is split into 8 detectors for the additional short-separation optodes with a distance of 0.8 cm from each source (NIRx Medizintechnik GmbH, Berlin, Germany) to account for superficial blood flow [43, 58]. We chose to measure cerebral blood flow in the prefrontal cortex region as working memory tasks (such as the n-back) predominately activate this region [59–61]. After dimming the lights, and headphones placed on the participant to minimize auditory distractions, system calibration will be performed before each assessment using NIRStar 15.2 software, and using the predefined montage; and the fNIRS signals will be visually quality checked and noted during data collection for motion artifacts or lost channels. Cerebral blood flow measures will be taken simultaneously while the participant performs 3 cognitive tasks of different workloads (numerical 1-, 2-, and 3-back tests). Our primary outcome variables will be changes in oxy-Hb between the 1-back and 2-back, and between the 1-back and 3-back tests. We will also record deoxy-Hb concentrations. The frontal border of the fNIRS cap will be placed about 2 cm above the nasion point and centered on the Cz, in order to capture prefrontal cortex blood flow changes. We chose to examine oxy-Hb because this signal has been previously shown to correlate with blood flow better than the deoxygenated signal [62], and is more highly correlated with the blood-oxygen-level-dependent (BOLD) fMRI signal [62, 63], although both will be reported.

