#### fNIRS calibration and data processing

Changes in cerebral blood flow (oxy-Hb) will be assessed using the MATLAB-based software NIRS Brain AnalyzIR toolbox (https://github.com/huppertt/nirs-toolbox) [64]. The data will be predicted on a block design, which is characterized by alternating periods of activity and rest to facilitate the acquisition of the fNIRS signals. Each trial will be preceded by 20 s of rest. Raw voltage will be converted to optical density, then to hemoglobin concentrations according to the modified Beer-Lambert law. After, the hemodynamic response function will be detected using an autoregressive model-based algorithm to solve for the general linear model (GLM), which allows for residuals of the GLM to be at random [65]. This approach uses pre-whitening filters using autoregressive models and employs iterative reweighted least squares, taking into account serial correlations, motion artifacts, and simultaneous regression of the short-separation channels. Gaussian functions will be used with a set standard deviation and separation of means according to the timeframe of the n-back task for the temporal basis of the function. First level statistics will be performed between each source-detector pair between the baseline (1-back) and the task conditions (2- and 3-back). False discovery rate (FDR) correction using a Benjamini-Hochberg procedure will be employed to correct for multiple comparisons at a critical level of < 0.05. Then, second-level group statistics will be performed on the regression coefficients obtained from the first-level statistics. Region-of-interest (ROI) statistics will be carried out to derive averages over all channels.

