#### Arterial stiffness and pulse wave velocity

Arterial stiffness (defined as augmentation index [AIx]) and pulse wave velocity (PWV) will be measured using a SphygmoCor XCEL PWA/PWV system (AtCor Medical, Sydney, NSW, Australia) [68]. The technology is non-invasive, reproducible, and accurate using the radial pressure waveform to calculate the aortic pressure waveform. The AIx can be derived from the aortic pressure waveform and is defined as the difference between the first and the second systolic peak. PWV is considered the gold standard method for assessing arterial stiffness. PWV is calculated by the formula: PWV (m/s) = distance between measurement location (m)/transit time (s) [69]. First, after 2 min supine rest, blood pressure and AIx will be determined. Then, the distance from the suprasternal notch to the carotid site, from the suprasternal notch to the femoral site (top of the leg cuff), and from the femoral pulse to the top of the leg cuff will be measured using a measuring tape. These distances will be subsequently used to calculate PWV. Three high fidelity pressure waveforms will be recorded using a carotid tonometer with a leg cuff to capture blood pressure waveforms at the carotid and femoral sites. The average of the three high-quality recordings will be used to determine PWV (m/s).

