### Statistical methods

Mixed effects models with subject as a random effect to assess within condition differences will be performed, and to examine time-by-condition interaction effects. Changes in arterial stiffness and PWV will be assessed in relation to cerebral blood flow changes in the mixed models.

Exploratory analyses will be performed excluding the short-separation regressors and ROI averages to compare to the main analyses.

Secondary outcomes (i.e., cognitive function, psychological factors, stress), will be assessed using mixed models, with the subject as a random effect, looking at both the within condition changes and the time-by-condition interaction effects. Correlational analyses will be performed to investigate the association between changes in cognitive function and cerebral blood flow if significant changes are seen. Maximum likelihood estimation will be used in the mixed models to handle missing data at random. Subsequent sensitivity analyses will be performed if necessary.

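### The statement that researchers cannot be blinded is too broad: its reason covers session staff, not offline fNIRS processing, the cortisol assay or the modelling

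*Protocol article*

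**What the plan says.** The blinding statement stands in the Familiarization visit section, in the paragraph on random ordering of the three conditions: "Researchers cannot be blinded in this type of study design or condition". The next sentence deals with access: "Researchers within the study will have access to the allocation sequence list and will retrieve the randomization code prior to each experimental day", and the stated purpose is "in order to prepare the laboratory equipment".

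Two quality judgements are described elsewhere. Under Cerebral blood flow, "the fNIRS signals will be visually quality checked and noted during data collection for motion artifacts or lost channels". Under Arterial stiffness and pulse wave velocity, PWV is the mean of three recordings described as high in quality, with no criterion given.

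The fNIRS calibration and data processing section describes cleaning as a regression method that "employs iterative reweighted least squares, taking into account serial correlations, motion artifacts, and simultaneous regression of the short-separation channels". Statistical methods adds: "Exploratory analyses will be performed excluding the short-separation regressors and ROI averages to compare to the main analyses", and also "Subsequent sensitivity analyses will be performed if necessary".

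Data management gives each participant a code for anonymity and does not mention condition labels. The Discussion considers awareness of condition for participants but not for researchers.

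**The concern.** The article takes a position and gives a reason, which is impossibility. That differs from leaving masked analysis to a document that is not shown. The reason applies to part of the team only. Someone who supervises a stepping break knows that it was a stepping break. Someone who fits a general linear model to a stored optical signal, or runs an ELISA plate, has no need to know.

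This matters because the hypotheses are directional by condition: oxy-Hb is expected to rise after active breaks, and to rise more with the higher intensity. An analyst who sees the labels knows which result is expected. Decisions that remain open after acquisition, such as how the noted channel problems are used or whether a sensitivity analysis is needed, would then be made with that knowledge. In a trial of 16 that is open at delivery, masking the offline work is an inexpensive safeguard, and the sentence as written excludes it.

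**Working it through.** The plan gives no figure on blinding, so the check sets the stated reason against each task in the article.

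**1. Tasks to which the reason applies**
- Delivering the chat, resistance or stepping break (Experimental conditions): staff see the condition. Masking is not possible.
- Visual fNIRS signal check (Cerebral blood flow): made live during data collection by staff in the laboratory. Relabelling files afterwards does not mask it.
- PWV recording (Arterial stiffness and pulse wave velocity): recorded, and apparently judged, in the session. Same conclusion.

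**2. Tasks to which it does not apply**
- fNIRS modelling (fNIRS calibration and data processing): run on stored signals. It needs to know which files share a condition, not which condition it is. X/Y/Z labels suffice.
- Cortisol assay (Other measures): samples are centrifuged, frozen and assayed by ELISA. Tubes can carry coded labels.
- Mixed models with time-by-condition interaction (Statistical methods): a three-level factor coded X/Y/Z gives the same fit and the same tests as one with named levels.

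**3. Access against its purpose**

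The allocation list is opened so that equipment can be prepared. That need ends when the session is set up, and no section extends it to processing or analysis.

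**4. Amount of recoding**
- Sessions: 16 participants × 3 conditions = 48.
- fNIRS recordings: 48 × 2 (before and after) = 96.
- Saliva samples per test day: 4 in the hour after waking + 1 before breakfast + 1 before and 1 after the 80 minutes = 7. In total 48 × 7 = 336, if all are provided.

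One mapping with 48 rows covers all of these.

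**5. Effect on the design calculation**

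None. Masking changes neither the 16 participants, nor alpha of 0.05, nor power.

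**The case against.** The strongest reply concerns scope. The sentence stands among the allocation procedures and is followed by a remark about preparing equipment, so it may have been meant for session staff only. This is also a condensed article whose analysis plan is not shown, so silence on masked analysis is no fault. Both points are fair and limit the finding to wording and a cheap addition. They do not remove it, because the sentence makes no exception and says that blinding cannot be done.

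A reader might go further and infer that condition-aware exclusions, or a condition-aware choice among pipelines, will distort the primary result. The document does not support this:
- Signal problems are noted, and no section describes excluding a channel, session or participant.
- The PWV text describes three recordings, not a choice from a larger pool, and PWV is not the primary outcome.
- Cleaning is algorithmic, which leaves less room for judgement.
- The variants without short-separation regressors and ROI averages are labelled exploratory, so the main analysis is named in advance. Reporting the best variant as primary would depart from the plan.
- No section says how files are labelled offline, so it is not established that processing is done with the condition known.

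It may also be objected that recoding achieves little while study researchers can open the list. That stands, and the fix has to deal with it.

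**Conclusion.** The statement is wrong as written for offline fNIRS processing, the cortisol assay and the mixed-model analysis, and correct for staff who deliver conditions and take in-session measurements. Severity is minor: a cheap improvement, not a demonstrated bias or a contradiction. The size of any bias cannot be estimated from the document, because it describes no exclusion step from which to calculate one.

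The conclusion assumes that the sentence means what it literally says, and that offline work can be done by someone who does not use the allocation list. If the sentence was meant for session staff only, one clarifying clause settles the wording, and the statement on coded labels is still worth adding.

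**What to change.** Limit the sentence to staff who deliver the conditions and take measurements in the session. Then add:
- Before offline processing, an existing team member recodes sessions and saliva samples to neutral condition labels (X/Y/Z).
- Whoever processes and models the data does not consult the allocation list. Files that reveal the condition, such as heart rate and perceived exertion during the breaks, are kept apart from the coded data.
- Any decision made after acquisition on noted channels or sessions, and the main model script, are fixed on the coded data before the labels are opened.

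The text should say plainly that the live fNIRS and PWV quality checks are not masked. Recruitment ended in January 2021, so if processing has already been done with labels open, the article or the results report should say so instead.

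The cost is a few hours of recoding by existing staff, a short delay before processing, and a few sentences of text. Conditions, measurements and sample size do not change.

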### Pre-experimental day monitoring

In order to standardize the 24 h prior to each test day, participants will be advised to abstain from any heavy physical activity and will be asked to record details about their physical activity and sleep in a standardized diary. Participants will also wear activity monitors during the 24 h prior to test day to collect data on physical activity and sedentary behavior (hip-worn Actigraph GT3X+ and thigh-worn activPAL micro) and sleep (wrist-worn Actigraph GT3X+). Physical activity and sedentary variables from the Actigraph will include total physical activity and percentages of wear time spent in sedentary, light, and moderate-to-vigorous physical activity, according to standardized cut-points [53]. Physical activity variables from the activPAL micro monitor will include time spent sitting including in prolonged bouts (> 20 min), number of breaks from sitting each hour and time spent standing, stepping, and intense stepping. During night time, participants will wear the Actigraph GT3X+ on their left wrist [54]. Using the most common algorithm for sleep-wake scoring in children developed by Sadeh et al. [55], the following key aspects of sleep will be calculated: time to sleep onset, sleep efficiency, times waking up after sleep onset, and total sleep. Diaries will also be filled in to provide complementary details on placement time of activity monitors, sleep timing, and sleep behavior.

In order to standardize dietary intake and blood glucose levels, participants will be asked to record their dietary intake for the 24 h prior to each condition in a standardized food diary and closely match their dinner for each pre-condition day. They will also be asked to fast and abstain from caffeine after dinner the night before. A researcher will call or message the parents the day before the pre-condition day to remind about physical activity behavior the day before testing, taxi ride, standardizing the dinner, saliva samples, and health state of the participant (e.g., no COVID-19 symptoms). After each laboratory visit, a researcher will call or message to ensure that no influenza symptoms have developed in the household of the participant.

### Experimental conditions

To minimize physical activity on the morning of the visit, participants will be transported to the laboratory via taxi. On the morning of testing, participants will be asked to provide four saliva samples (for cortisol testing); immediately after waking up and at 30, 45, and 60 min thereafter. Once the participants arrive at the laboratory, a practice session of the cognitive tests will be performed, a saliva sample will be taken, and then a time-restricted, individually standardized breakfast (based on their food choices decided at the familiarization visit) will be provided. Participants at their initial visit will be advised to eat their preferred amount, which will be subsequently weighed and recorded. The portion sizes will be replicated at each visit. The activPAL activity monitor will be worn during the experimental conditions to monitor sitting time during the test day. Participants will be equipped with a chest strap heart rate monitor to be worn during the whole test day visit. After breakfast, pre-condition outcome measures will be collected.

The three experimental conditions (summarized in Fig. 1) are (A) 80-min prolonged sitting with 3-min seated social breaks every 17 min (SOCIAL), (B) 80-min sitting with 3-min bouts of simple resistance activities every 17 min (SRA), or (C) 80-min sitting with 3-min bouts of moderate-intensity stepping every 17 min (STEP). During sitting, participants will be permitted to read a book, do schoolwork (from a laptop is permitted), and drink water, but not doze off or play games. The SOCIAL break (condition A) will consist of a 3-min chat between a research staff member and the participant while seated. For the SRA break (condition B), participants will be asked to complete 20-s body weight half-squats, 20-s calf raises, and 20-s gluteal contractions and knee raises repeated three times in sequential order by following standardized video instructions (as per [56]) with music. The STEP break (condition C) will be performed at moderate intensity at a pre-determined pace (around 110 beats per minute), using a standardized step (27.5 cm) following a standardized video with music in order to achieve a heart rate substantially higher than the SRA break. Toilet breaks and duration of the breaks will be recorded. Heart rate will be measured during the 80 min intervention at the 2:50 min time point during each break, and rate of perceived exertion (RPE) based on the Borg scale [57] will be evaluated immediately following each break. Heart rate will also be assessed once at the start of the first 1-back of the cognitive test (Fig. 2). In order to reduce the spread of COVID-19, certain hygienic and protective regulations and procedures will be followed. Details can be found in Additional file 1.

**Fig. 1 Fig1:**
[figure not shown]
Experimental day procedures of the three conditions, including pretests, the 80-min intervention, and post-tests. FNIRS will be measured while participants perform working memory tests (*n*-back). Condition A: prolonged sitting with 3-min seated social breaks every 17 min (SOC); Condition B: prolonged sitting with 3-min simple resistance activities every 17 min (SRA); Condition C: prolonged sitting with 3-min step-up activities every 17 min (STEP). fNIRS, functional near-infrared spectroscopy; PWA, pulse wave analysis; PWV, pulse wave velocity

